### Randomisation

After enrolment, children will be block randomised into pairs according to their activity level at House Functional Classification System [36,37] (grade 6-8 vs 4 or 5) using a computer generated set of random numbers. A computer random allocation will also be used to randomly assign the subjects of each pair to experimental or control group by a computer random allocation. We choose a matched pairs design because it minimises the likelihood of group differences at baseline that has often been present in UL rehabilitation studies [39]. All randomisation, sequence generation, and preparation of group allocation materials will be performed by a third party, who has no direct contact with the clinical aspects of the trial. The master list of random numbers will be located in locked cabinets only accessible at completion of the RCT for analysis.

### Blinding

In order to make blind the study the children enrolled and their parents will be informed about general description of the design of the study, so that they know that there are two parts during the treatment, one of observation and one of action, but not the kind of observation. Outcome measures (Melbourne Assessment of Unilateral Upper Limb Function and AHA) will be videotaped, randomised and scored by assessors blind to group allocation and order of assessment. The treating therapists and study personnel, committed to help during the treatment, will be not blinded of group allocation. Outcome measures will be administered by a therapist blind of group assignment and scored by different assessors also blind to group allocation.

### Therapy protocols

The group of physical therapists and child neurologists planned 15 sets of daily life UL exercises. Each set is composed by three sequential UL goal actions of increasing complexity. The first 8 sets are unimanual exercises (total of 24), while the last 7 sets bimanual (total of 21) where the two upper limbs have different roles in an integrated action. In order to grade the activities with the range of children capabilities two series of sets were conceived, one for children grade from 6 to 8 at House Functional Classification System [36,37] and one for those grade 4 or 5. The setting of all exercises is the same but the proposed type of movement (i.e. range of movement) is simplified for the children with more severe impairment (grade 4 or 5). Each action of the two series performed by an actor was videotaped so that the videos showed only the hand and arm and in the first perspective; then each of this videos was edited so that each lasted 3 minutes. The actor used one or two hands respectively for the unimanual and bimanual exercises; collected videos were also tipped over, in order to have the same videos for the right and for the left hand. Moreover, 15 sets of computer games with no biological movements were chosen (i.e. quiz games, crossword, Simons etc.).

### Study treatment

The total dosage of intensive rehabilitation will be 15 hours. Each daily session will last 60 min with a total of one session for 15 consecutive working days. During the rehabilitation sessions, children will be sitting on a chair with their arms placed on a table; to provide a suitable freedom range of movement of upper limbs, the child's chair will be adjusted so that the table is at waist height. A large monitor screen (22 inches) will be positioned 1-m distance in front of them. A member of the staff will sit on the child's affected side in order to prevent the children from leaving the table, to assist them in maintaining attention on the video sequences or videogames and during the execution of the task. Another person of the staff will operate the setup (on/off of the monitor, use of keyboard, arrangement of the setting on the table).

The children randomised in the experimental group ("action observation therapy") will watch the video sequence and afterwards the same objects shown on the video will be placed on the table and the children will be requested to perform the observed action for 3 min with their hemiplegic UL or both limbs, as demonstrated on the video. Each video sequence will be presented twice during the training (Figure 2).

**Figure 2 F2:**
[figure not shown]
**Layout of Study Treatment**.

Children randomised in the control group will match the design of experimental session except for the content of the videos showing computer games with no biological movements (Figure 2). Moreover, the children will play the games without using their hands, i.e. the person of the staff will use the keyboard to go on over the game. Following verbal instruction given by the staff, control group will carry out the same exercises in the exact order performed by the experimental group.

### Outcome measures

#### - Classification of the sample

The children entered into the study will be classified according to:

##### - House Functional Classification System

This is a reliable tool for assessing upper extremity function in children with CP [36,37]. It was developed for the evaluation of function in the affected hand after surgery for thumb-in-palm deformity in children with spastic hemiplegic CP [36] and has been used to evaluate children before and after upper extremity BoNT-A injections [40]. Even if it was constructed for hemiplegic CP, in some studies it is used for each hand separately in all types of CP through observation of the child in activities requiring bimanual hand function [41]. The classification consists of 9 grades ranging from a hand that is not used at all (grade 0) to one that is used spontaneously and independently from the other hand (grade 8). The House has been reported to have an excellent interrater (Intraclass Correlation Coefficient, ICC = 0.92) and intrarater reliability (ICC = 0.94) [37].

#### - Primary and secondary outcome measures

On the basis of our scientific hypothesis, the primary outcome measure of interest is bimanual UL activity performance using the AHA. Secondary measures include measure of unimanual capacity (Melbourne Assessment of Unilateral Upper Limb Function, MUUL) and the bimanual daily activities at home and in the community (ABILHAND-Kids). At the beginning of the study we intended to use also the Jebsen-Taylor Hand Function Test [42], but we realised that the test could be frustrating for some children with more severe impairment and, since the measure of dexterity was not an aim of our proposed rehabilitative approach we decided to skip this test from our measures.

##### - Assisting Hand Assessment (AHA)

The primary outcome was the Assisting Hand Assessment (AHA, version 4.4) that is a standardised, performance-based test for use with children aged 18 months to 12 years, who have an unilateral upper limb impairment. It evaluates the spontaneous use of the assisting hand during a semi-structured 10-15 minutes play session with specific toys (from the AHA test kit) requiring bimanual handling [43,44]. The play context is age appropriate so there is one context for children 18 months to 5 years (Small kids AHA) and others (two different board games) for children aged 6-12 years (School Kids AHA). The forms are directly comparable as demonstrated by a test-retest of alternate forms of AHA [45]. The AHA is videotaped in a standardised manner and the subsequent scoring procedures produce a raw sum score ranging from 22 (low ability) to 88 (high ability) and a logit measure from -10.18 to +8.70. The AHA can only be administered and scored by a certified rater. Interrater, intrarater and test retest reliability of the AHA have a high ICC [45,46]. The Smallest Detectable Difference (SDD) over time indicated that a change in School Kids AHA scores from one test session to the next must be 3.65 sum scores (0.76 logits) or more to be considered a true change with 95% probability [45]. Also, the scale responsiveness to change was demonstrated in intervention studies focusing on forced use therapy [47], CIMT [38,44,46,48,49], HABIT [50] and, recently, modified CIMT followed by task-specific training of goal-directed bimanual play and self-care activities [51,52].

##### - Melbourne Assessment of Unilateral Upper Limb Function (MUUL)

The MUUL is an evaluative tool that measures unilateral upper extremity quality of movement in children with neurological impairments aged from 5 to 15 years [53,54]. A modified MUUL for children in the age range of 2 to 4 years has recently been developed [55]. MUUL is a criterion-referenced test based on 16 items scored on a 3- to 5-point ordinal scale comprising tasks that are representative of the most important components of unilateral UL function (reach, grasp, release, and manipulation). Most items are further subdivided in 2 to 4 sub-items (total of 37 sub-items) that represent an aspect of the required movement, such as range of movement, fluency, target accuracy, speed, and quality of movement. The total score can range from 0 to 122 points and can be converted to a percentage. According to International Classification of Functioning, Disability and Health (ICF) the MUUL measures both capacity in the domain of activity and some aspects at the body functional level (i.e. range of motion, fluency) [46]. The test is administered with the child's performance recorded on videotape for subsequent scoring. The interrater reliability for the total score is 0.97 (ICC). Percentage of agreement of 32 sub-items varied between 35% and 95%. The intrarater reliability is also high (ICC 0.97) [56]. In the first reliability study of MUUL, Randall et al [53] demonstrated that when two assessments of the same child scored by the same therapist differ by more than 14.3 points (12%) it is probable that it reflects a true change in function rather than an error in measurement. Recently, Klingels et al [55] demonstrated that the SDD is 8.99% instead of 12%. The MUUL has been used in several intervention studies [57-59] but some studies have suggested that the MUUL might not be sufficiently sensitive to changes brought about by BoNT-A treatment because the SDD was smaller than recommended. Therefore, further investigations were warranted [40].

##### - ABILHAND-Kids

The ABILHAND-Kids is a short questionnaire that measures 21 mainly bimanual daily activities referred to the activity domain of the ICF. The difficulty experienced by the child to perform the required tasks is scored by a parent on a 3-point ordinal scale (impossible, difficult, easy). It has been validated and calibrated in children with CP (age 6-15) and has a high reliability (R = 0.94) and a good reproducibility over time (R = 0.91). The questionnaire was developed using the Rasch measurement model which provides a method to convert the raw scores into a linear measure located on a unidimensional scale [60]. In a recent study where a modified CIMT followed by task-specific training of goal-directed bimanual play and self-care activities were used in children with HCP a high effect size (Cohen's d: 1.01) was reported [46,51,52].

### Brain Reorganization

Some of us [61] recently have performed a study using fMRI to explore the activation of human anterior intraparietal area (AIP) during the observation of complex object-manipulation tasks (e.g. inserting a key in a lock and turning it) as compared to simple tasks (e.g. whole hand grasping of an object) executed with the left and the right hand in a first person perspective. The results showed that, in general, both complex and simple tasks produced an activation of the fronto-parietal mirror system and that the activity of AIP in each hemisphere was higher during observation of the contralateral hand (hand identity effect). A Region-Of-Interest (ROI) analysis of the parietal activations responding to hand identity showed that each AIP was more active during the observation of complex with respect to simple tasks. In the right AIP this effect was stronger during observation of the contralateral hand, in the left AIP was stronger during observation of both hands. This complexity related property was not observed in the other activated areas. These findings support the concept that the observation of motor acts retrieves the internal representation of those same acts in the observer's motor system (direct-matching hypothesis based on the mirror neuron mechanism). This study was conducted in adults, but our group have large experience in performing fMRI with children [62-67]. To obtain a better compliance by the children the paradigm used with the adults was reduced in the time of acquisition and only two functional series (see later) will be acquired.

The main aims of this part of the study will be:

• to explore the MS in children with HCP and

• to provide, if there are, some evidences of plastic changes after action-observation training either on the MS or in the somatosensory cortex.

To verify the first hypothesis, a group of healthy age-matched children will be enrolled. For the second hypothesis, a subgroup of children with HCP recruited for the study and randomised to the experimental or control group (see inclusion criteria) will perform fMRI before (T0) and after the training (T1 and T2) (see Figure 1).

#### - fMRI: experimental design

From the activation methods of our previous study [61], a set of 12 video-clips showing object manipulation, lasting 8 seconds each, will be used in this experiment: 3 complex actions and 3 simple actions, performed with the right or the left hand. The observed hand will be presented in a first person perspective. The complex actions are: i) grasping little cubes to put into a box, ii) performing a simple scale on a piano keyboard, iii) grasping a key, putting it into a lock and turning it. The simple actions consisted in a whole hand grasping of a small box in the same visual context as the corresponding complex actions. The two sets (simple and complex) of clips are perfectly balanced as to the visual content (luminance, amount of visual information). The arm trajectory is the same for both simple and complex actions. The observation of the static initial frame of each clip is used as control condition. The experiment will be performed using a block design format and it will consist of 2 functional series containing all the three types of action ("mixed" condition). In each functional series, four conditions are codified: simple tasks performed by the right hand (SR), simple tasks performed by the left hand (SL), complex tasks performed by the right hand (CR), complex tasks performed by the left hand (CL). Each series presents two blocks for each condition, in random order and in a counterbalanced manner, interleaved with as many control blocks. For each functional series each block consists in the presentation in random succession of the three different types of action corresponding to the same condition. The stimuli will be presented binocularly, displayed on LCD goggles (VisuaStim XGA - Resonance Technology, USA). Children will be instructed to observe the video-clips, maintaining fixation in the middle of the screen. The maintenance of the fixation will be confirmed by continuously monitoring gaze through an infrared camera, mounted inside the goggles (sample frequency 60 Hz). Moreover, in the same MRI session, children will perform also another fMRI study using a sensory-motor task, alternating sensory stimuli and motor stimuli; the former consisting in the palm and fingers passively brushed by an external operator by means of a wooden spatula, at a frequency of about 1 Hz, while in the motor task, we will ask to the children sequentially moved all the fingers in opposition to the thumb ("open and close your hand"). One series for each hand will be acquired. We will start with the unimpaired hand to check that the children have understood the task and that they remember it. The subjects will be asked to keep their eyes closed; ambient scanner noise will be constant throughout baseline and activation periods, and attenuated by occlusive ears plugs.

#### - fMRI: Image acquisition, processing and analysis

Blood oxygen level dependent (BOLD) responses will be acquired by a 1.5 T MR system (General Electric Signa Horizon LX Milwaukee, USA), equipped with echo-speed gradient coil and amplifier hardware. Activation images will be acquired using Echo Planar Imaging (EPI) gradient-recalled echo sequence (TR/TE/flip angle = 3000 ms/50 ms/90°, FOV = 240 × 240 mm, matrix = 64 × 64, 5 mm thick slices). For MS exploration, time-course series of 132 scans for each volume will be collected in 16 blocks alternating between control and action conditions, resulting in an acquisition time for each series of 6'36'', repeated 2 times. For motor-sensory tasks, time curse series of 100 scans for each hand will be collected in 16 blocks alternating between Motor and Sensory conditions (each followed by a period of Rest), resulting in an acquisition time for each series of 5'00''. Each first block of each series included 4 initial extra scans to allow the stabilization of signal and this period will be eliminated from subsequent analysis. A volumetric set of data (3D FSPGR: TR/TE/TI/flip angle = 21.1 ms/3.8 ms/700 ms/10°; FOV = 280 × 280 mm, matrix = 256 × 256) will be also acquired to generate a 3D whole brain reconstruction. Data analysis will be performed using the Brain Voyager QX software package (Brain Innovation, Maastricht, the Netherlands). Before statistical analysis, raw data will be corrected for head movements and high-temporal filtered in order to exclude temporal drifts. For each subject, all the two-dimensional functional data will be co-registered, concatenated, aligned to the three-dimensional high-resolution images and finally transformed into Talairach space [68]. A General Linear Model (GLM) approach will be used to generate statistical parametric maps, using a hemodynamic response function modelled on the standard Boynton's function [69] and considering the four conditions: SR, SL, CR, CL. Moreover, because the side of HCP in the children enrolled could be right or left, to correct this effect, we will treat the processing delivered by the dominant hand as the unimpaired hand and whose by the non dominant hand as the impaired hand. A ROI analysis will be conducted on the statistically significant clusters coming out from the application of the GLM analysis. In these ROIs, a single-subject analysis will be also performed measuring the average per cent signal change of each individual subject.

To test our experimental hypotheses we plan these main analyses, as follows:

• to investigate whether the used stimuli is able to activate the MS in children with HCP, we will contrast activity for all the observed actions vs the static conditions (hand action observation, all stimuli > static conditions) and if the activity in children with HCP will be different with respect to normal functional response (healthy children);

• to explore whether there are areas differentially responding to the identity of the observed hand, we will compare the activity related to observation of the simple and complex tasks performed by the corresponding impaired (non-dominant) hand with those performed by the unimpaired (dominant) hand;

• to study whether there are some changes after UP-CAT, a group analysis of intra-participant change in activation will be undertaken using a ROI approach both for MS and for the sensory-motor task.

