An important assumption for an observation-based therapy is the plasticity of the MS. Several studies [24-26] indicate a strong role of the MS in representing previously acquired motor skills. These fMRI studies examined the mirror activations in person expert in specific motor skills (dance) and compared them with the activations determined by the same stimuli in individuals having different motor experience. The results showed that the observed dance steps were mapped onto the observers' premotor-parietal motor system and that the activation was stronger in individuals expert in performing them. Thus, during observation, observers tend to 'resonate' more strongly with actions already embodied in their own motor repertoire.

These data prompt the hypothesis that if observation is accompanied by imitation one should expect a higher activation of the MS. In a fMRI study where non-guitarists were asked to imitate unfamiliar guitar chords (a task chosen to represent the initial stage of imitation learning) Buccino et al [27] demonstrated that the basic circuit underlying this capacity includes the MS that starts to be active during the observation of the guitar chords and it is permanently active also during motor preparation and execution. Moreover, the left dorsolateral prefrontal cortex (DLPFC, most likely area 46) was found activated mainly during motor preparation of imitative execution, suggesting its possible role in the selection and recombination of the individual motor elements, as represented in the MS, into a new motor pattern.

These findings were confirmed by a more recent study conducted by Vogt et al [28] showing that MS is more strongly involved during the observation of novel actions than of previously practised actions.

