The possibility to use for neurological patients an observation/imitation approach in the Action-Observation Therapy has been exploited in two studies with hemiplegic adults after stroke. In the first clinical trial, Ertelt et al [29] enrolled 16 participants with moderate post-stroke hemiparesis who were randomly assigned to either the experimental or the control group. The experimental group performed an action-observation training based on the combination of action observation with repetitive motor training of the observed actions for 90 minutes per day with the paretic hand. Actions of increasing complexity were observed and imitated each day for 18 days. The control group performed the same UL actions of the experimental group on verbal instruction, while they observed only geometrical symbols and letters. Significant functional improvement on standard scales occurred for experimental group compared with controls and was maintained at 8 weeks post-training. In addition, before and after training, participants of both groups performed an independent object manipulation task while scanned with fMRI. The data revealed, only in the experimental group, a significant increase in neural activity of motor-related brain regions including the MS. More recently, Franceschini et al [30] performed an observational study, without control group, with twenty-eight chronic stroke patients with UL impairment. All patients underwent for four weeks, five days a weeks, a rehabilitation treatment based on observation of video-clips presenting hand daily actions, followed by the imitation of those same actions with the affected limb. In all function scales, scores improved significantly after treatment and changes were maintained also after two-months.

To date, there are no studies using action-observation model in children. In this project, we will propose, for the first time, a new paradigm of UL rehabilitation, called Upper Limb Action-Observation Training (UP-CAT), built as a randomised controlled trial (RCT) according to Consolidated Standards of Reporting Trials (CONSORT) Statement for Randomised Trials of non-pharmacologic treatment guidelines [31,32] to examine the efficacy of Observation To Imitate (OTI) in improving the UL activity in children with Hemiplegic Cerebral Palsy (HCP).

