## Methods/Design

The following hypotheses will be tested by means of a RCT comparing the effects of UL action observation versus physical practice in improving the UL activity in children with HCP:

• If the MS works in terms of action goals, regardless of the kinematic properties, there will be a better improvement in the goal of UL use rather than in the kinematics of UL;

• OTI will be able to induce more changes in UL activity than those due only to the physical practice of the same actions;

• OTI will result in greater enhancement of daily activity performance;

• OTI will result in a greater mirror circuit re-organisation compared to action execution only and this cortical plasticity will be retained for longer periods.

These experimental hypotheses will address the following specific aims:

• OTI model is a novel training method where the main core is to observe an UL performing tailored goal actions, with the intent to imitate. This study will determine if this model is useful to enhance activity performance and, if there are improvements, for how long that effect will be retained;

• If OTI model will enhance the activity performance, new models of the rehabilitation setting in clinical practice will be proposed;

• If OTI model results in greater brain plasticity, the functioning of MS and its role in learning also in children with brain lesion will be demonstrated;

• If OTI model will be a good tool, it will guide practice also in other disabilities.

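### The planned fMRI test of the mirror-reorganisation hypothesis looks for unspecified change and names no between-arm contrast, region or decisive visit, so it does not match the comparative hypothesis

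*Protocol article*

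**What the plan says.** **Hypothesis (Methods/Design, fourth hypothesis).** "OTI will result in a greater mirror circuit re-organisation compared to action execution only and this cortical plasticity will be retained for longer periods". This has two parts: a comparison between arms, and retention. The aims that follow add that, if OTI gives greater brain plasticity, the working of the mirror system (MS) and its role in learning in children with brain lesions will count as demonstrated.

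**Planned test (fMRI: Image acquisition, processing and analysis, closing list).** The list is introduced as the analyses that test the experimental hypotheses. Its third item is the only one about change: "to study whether there are some changes after UP-CAT", for which "a group analysis of intra-participant change in activation will be undertaken using a ROI approach both for MS and for the sensory-motor task".

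**Regions (same section).** "A ROI analysis will be conducted on the statistically significant clusters coming out from the application of the GLM analysis".

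**Visits (Brain Reorganization).** A subgroup of children from both arms is scanned at T0, T1 and T2. Neither post-training visit is given priority.

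**Direction (Background).** In the dance studies, "the activation was stronger in individuals expert in performing them". A later study is cited as showing that "MS is more strongly involved during the observation of novel actions than of previously practised actions". The same part of the Background expects higher activation when observation is joined with imitation, and the adult stroke trial is reported to show "a significant increase in neural activity of motor-related brain regions including the MS" in the experimental arm only. No direction is carried into the hypothesis or the analysis list.

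**The concern.** The hypothesis asks whether OTI changes the mirror circuit more than execution alone. The analysis asks whether anything changed within children. These are different questions. A change shared by both arms, from practice, maturation or familiarity with the scanner, would satisfy the second and say nothing about the first.

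Several other choices are also left open: which clusters, which of two tasks, which of two visits, and which sign. Each adds a way for noise to be read as plasticity. What is at stake is the mechanistic claim in the aims, which is worded strongly. The primary outcome, the Assisting Hand Assessment (AHA), is not affected.

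**Working it through.** **The plan's own figure.** The only calculated figure in the article is 12 per group for the AHA (Sample size: effect size 1.16, 0.05, 80% power). It reproduces by the normal approximation: 2 × (1.960 + 0.842)² / 1.16² = 15.70 / 1.3456 = 11.7, i.e. 12. It has no bearing here, since no figure is given for the fMRI hypothesis.

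**Hypothesis and test side by side.**

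| Element | Fourth hypothesis | Planned change analysis |
|---|---|---|
| Comparison | OTI against execution only | change within children; no between-arm contrast |
| Region | mirror circuit | clusters found significant in the GLM; number and place not fixed |
| Task | mirror circuit only | mirror task and sensory-motor task |
| Visit | retention is part of the claim | T1 and T2, neither decisive |
| Direction | greater reorganisation, no sign | unspecified change |

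The sign is not left open throughout that list. Its first item states one (observed actions above static frame), so the authors give a direction where they hold one.

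**False-positive chance if nothing changes.** Inputs:
- Regions: the Background names the inferior parietal lobule (IPL) and ventral premotor cortex (PMv), plus the caudal inferior frontal gyrus (IFG). That makes three.
- Visits: T1 and T2.
- Hemispheres: one or two (assumption).
- Significance level: 0.05 two-sided. This is an assumption, because the 0.05 in Analyses is given for the clinical data.

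For m independent tests the chance of at least one false change is 1 − 0.95^m. With correlated tests it is lower; the correlated columns come from a simulation of equally correlated normal statistics.

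| m | Make-up (assumed) | Independent | r = 0.3 | r = 0.5 | r = 0.7 |
|---|---|---|---|---|---|
| 6 | 3 regions × 2 visits | 1 − 0.95^6 = 26.5% | 24.0% | 20.8% | 16.4% |
| 12 | 3 regions × 2 hemispheres × 2 visits | 1 − 0.95^12 = 46.0% | 39.8% | 32.0% | 23.1% |

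**How much is due to the open sign?** If one sign is named in advance, each test has a 0.025 tail.
- 6 tests: 1 − 0.975^6 = 14.1%, against 26.5%.
- 12 tests: 1 − 0.975^12 = 26.2%, against 46.0%.
- One test: 2.5% in the named direction, 5% two-sided.

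From 12 open tests, naming the sign alone brings 46.0% down to 26.2%. Naming one region summary and one visit alone brings it down to 5%. The open choice of region and visit matters more than the open sign.

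**What these figures leave out.** They assume no change in either arm. If both arms change equally, the hypothesis is still false, yet a within-child analysis would find change as often as its power allows. No multiplicity adjustment cures that; only a between-arm contrast does.

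**The case against.** **This is an exploratory substudy.** It uses a subgroup, and Brain Reorganization words its aims cautiously. Thresholds and multiplicity handling may well sit in a full protocol or analysis plan that is not shown. This stands: their absence is not the point, and the error rates are only illustrative. What remains is that the article itself presents this list as testing its hypotheses, and the item it gives for change does not match the hypothesis.

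**A group analysis may mean a comparison of groups.** This is possible, but the text does not say so. The same section uses single-subject analysis as the counterpart, which suggests pooling across children.

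**Stronger readings that the article does not support.**
- A reader might infer that a change of either sign in any cluster at either visit would confirm the hypothesis. It would not: "OTI will result in a greater mirror circuit re-organisation compared to action execution only" is a comparison, and retention is also required. An equal change in both arms, a change outside the mirror circuit, or one lost by T2 would all fall short.
- A reader might infer that the Background predicts both a rise and a fall. The fall is only an inference from a comparison of novel with practised actions. The one expectation stated outright is higher activation. Nor does the article say that the 12 scanner clips show the trained actions.
- A reader might take the adult trial's increase as the sign for this test. Those patients were scanned while manipulating objects, not while observing actions, so the sign does not transfer directly.
- A reader might add the sensory-motor regions to the test count. They do not test a mirror-circuit hypothesis, so they are left out above.

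**A two-sided test is legitimate.** Agreed, and the fix keeps it.

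**Conclusion.** The point holds as a mismatch between hypothesis and test. A comparative claim about the mirror circuit, with a retention clause, is to be tested by unspecified within-child change in clusters selected from the data, with no contrast between arms and no decisive visit. Followed as written, the analysis could not soundly support the conclusion that the aims attach to it.

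The illustrative chance of at least one false change is 16–26% for 6 tests and 23–46% for 12. This rests on assumed test counts, an assumed two-sided 0.05 for fMRI, and pairwise correlations from 0 to 0.7. The missing between-arm contrast is established from the text alone and does not depend on these figures. The matter is worth correcting, but it is confined to a secondary imaging hypothesis.

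**What to change.** In the closing list of the fMRI analysis section, replace the third item with one named test of the fourth hypothesis:

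- **Contrast:** OTI minus control, in the change from T0 to T1.
- **Measure:** per cent signal change for observed actions against the static frame.
- **Regions:** IPL and PMv/IFG, named in advance and not chosen from the change data, averaged to one value per child so that there is one test.
- **Sidedness and direction:** two-sided. State the expected direction and the background finding it rests on, and report an opposite-signed result as not supporting that expectation.
- **Retention:** test the same contrast at T2 second, for the retention clause.
- **Everything else:** label other clusters, other conditions and the sensory-motor task exploratory, or adjust them by Holm or a false-discovery-rate procedure.

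The cost is wording only. Children from both arms are already to be scanned at all three visits, so no new scans are needed. The downside is that findings in other regions or tasks carry less weight.
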